## Abstract

**Background:**

While simple Audit & Feedback (A&F) has shown modest effectiveness in reducing low-value care, there is a knowledge gap on the effectiveness of multifaceted interventions to support de-implementation efforts. Given the need to make rapid decisions in a context of multiple diagnostic and therapeutic options, trauma is a high-risk setting for low-value care. Furthermore, trauma systems are a favorable setting for de-implementation interventions as they have quality improvement teams with medical leadership, routinely collected clinical data, and performance-linked to accreditation. We aim to evaluate the effectiveness of a multifaceted intervention for reducing low-value clinical practices in acute adult trauma care.

**Methods:**

We will conduct a pragmatic cluster randomized controlled trial (cRCT) embedded in a Canadian provincial quality assurance program. Level I–III trauma centers (*n* = 30) will be randomized (1:1) to receive simple A&F (control) or a multifaceted intervention (intervention). The intervention, developed using extensive background work and *UK Medical Research Council* guidelines*,* includes an A&F report, educational meetings, and facilitation visits. The primary outcome will be the use of low-value initial diagnostic imaging, assessed at the patient level using routinely collected trauma registry data. Secondary outcomes will be low-value specialist consultation, low-value repeat imaging after a patient transfer, unintended consequences, determinants for successful implementation, and incremental cost-effectiveness ratios.

**Discussion:**

On completion of the cRCT, if the intervention is effective and cost-effective, the multifaceted intervention will be integrated into trauma systems across Canada. Medium and long-term benefits may include a reduction in adverse events for patients and an increase in resource availability. The proposed intervention targets a problem identified by stakeholders, is based on extensive background work, was developed using a partnership approach, is low-cost, and is linked to accreditation. There will be no attrition, identification, or recruitment bias as the intervention is mandatory in line with trauma center designation requirements, and all outcomes will be assessed with routinely collected data. However, investigators cannot be blinded to group allocation and there is a possibility of contamination bias that will be minimized by conducting intervention refinement only with participants in the intervention arm.

**Trial registration:**

This protocol has been registered on ClinicalTrials.gov (February 24, 2023, #NCT05744154).

**Supplementary Information:**

The online version contains supplementary material available at 10.1186/s13012-023-01279-y.

Contributions to the literature
We will test a low-cost, pragmatic de-implementation intervention that can be adapted to other trauma systems in high-income countries.Our trial will advance knowledge in de-implementation science by documenting barriers, facilitators, and strategies for successful implementation.Reducing low-value trauma care may reduce adverse events for patients and free up healthcare resources.

## Background

Low-value clinical practices are *tests or treatments that are not supported by evidence and may cause unnecessary harm *[1]. They expose patients to adverse events such as avoidable irradiation, postoperative complications, medication or transfusion side effects, unnecessary interventions on incidental findings, and direct and indirect expenses [2–5]. They are also a major barrier to timely access to appropriate care and threaten the sustainability of modern healthcare systems [2–4]. Stakeholders in high-income countries have expressed the urgent need to develop strategies to address the burden of low-value care with interventions targeting de-implementation [6–9]. De-implementation is defined here as *discontinuing or abandoning practices that are not proven to be effective, are less effective or less cost-effective than an alternative practice, or are potentially harmful *[10, 11].

Audit & Feedback (A&F), *a summary of the clinical performance of healthcare provided over a specified period of time*, has been shown to have a modest effect on the de-implementation of low-value practices [12]. Organizations such as National Audit Commissioners advocate for enhancing A&F to support clinicians in their use of feedback data [13, 14]. Theory and evidence, largely based on the implementation of *high-value *practices, suggest that multifaceted interventions addressing determinants for success (barriers and facilitators) may be more effective and cost-effective than simple A&F [12, 15, 16]. However, the mechanisms for change, barriers, and facilitators for de-implementation differ from those for implementation [16, 17]. As such, studies on the effectiveness of interventions designed to increase *high-value* care may not be generalizable to the reduction of *low-value *practices. There is therefore a need for research on the incremental effectiveness of multifaceted interventions over simple A&F for de-implementation [18]. Additionally, although the barriers and facilitators of de-implementation have been well documented [17, 19], experts acknowledge the critical need for research on the effectiveness of interventions tailored to these determinants for success to support the de-implementation of low-value practices [17, 20–23].

Injury is the leading cause of productive life years lost and is second only to heart and stroke disease for in-patient costs [24]. Given the need to make rapid decisions in a context of multiple competing diagnostic and therapeutic options, trauma care is a high-risk setting for low-value care. Trauma quality assurance programs in place in Canada [25–29] and worldwide [30–32] have been associated with improvements in quality of care [33–35], but they are based on simple A&F and exclusively target adherence to *high-value *clinical practices. Low-value practices in trauma care are frequent, subject to significant inter-hospital variation [36, 37], and are associated with increased complications, length of stay, and in-patient costs [36]. Trauma systems are a favorable setting for de-implementation interventions as they possess many documented facilitators including quality improvement teams with medical leadership, routinely collected clinical data, and performance linked to accreditation [19]. Furthermore, potential gains are huge due to the resource-intensive nature of trauma care. Trauma systems are thus the ideal setting to advance knowledge on de-implementation of low-value care.

Our primary objective is to assess the effectiveness of a multifaceted intervention embedded in a provincial quality assurance program compared to simple A&F to reduce low-value adult acute trauma care. Secondary objectives are to (i) identify the mechanisms associated with a successful implementation of the intervention, (ii) evaluate whether intervention effectiveness changes over time, (iii) assess the effect of the intervention on clinical outcomes and resource use, (iv) assess unintended consequences, and (v) evaluate cost-effectiveness.

## Methods

This protocol is reported according to the Standard Protocol Items: Recommendations for Interventional Trials (SPIRIT) statement (Additional file 1) [38] and the Consolidated Standards of Reporting Trials (CONSORT) extension for cluster trials (Additional File 2) [39].

### Trial design

We will conduct a parallel arm, pragmatic, superiority cluster randomized trial (cRCT). The trial is pragmatic as it is embedded in a Canadian provincial trauma quality assurance program. The trial scored 5/5 on 6 of the 9 domains of the PRagmatic Explanatory Continuum Indicator Summary (PRECIS 2) tool, 3/5 for organization intervention and 4/5 for the outcome, indicating a high level of pragmatism (Additional file 3: Table S1) [40]. As the trial will be based on routinely collected data that are available at no extra cost, we will use a baseline observation period pre-randomization to increase study power [41]. We will randomize at the trauma center level because quality programs operate at the local trauma committee level in each trauma center. A stepped wedge design will not be used as the minimum 1-year rollout period is unacceptably long for stakeholders and parallel arm cRCTs have fewer risks of bias than stepped wedge cRCTs [42].

### Setting

The trial will be embedded in the *Québec Trauma Care Continuum*, a provincial regionalized trauma system comprising 57 adult trauma centers of which 3 are level I (highly specialized urban centers), 5 are level II (similar capacity to level I but in smaller cities), 22 are level III (hospitals in small towns transferring most major trauma to level I/II centers after stabilization), and 27 are level IV (rural community hospitals). All centers undergo periodic verification in line with designation, conducted by the *Institut national d’excellence en santé et services sociaux* (*INESSS*) and overseen by the Ministry of Health and Social Services [43]. Verification includes simple A&F on adherence to *high-value* care and risk-adjusted outcomes and submission of an action plan within 6 months of reception of the A&F report. Local trauma committees in each center are required to ensure the quality of the trauma program according to designation requirements. Committees include the program medical director (chair), the program manager, heads of critical care, emergency and surgical departments, and multidisciplinary services, and a hospital administrator. Quality improvement activities include trimestral committee meetings with chart review and discussions with clinical and administrative leads locally and at referring centers to identify improvement strategies such as the development of local care protocols. Formal letters of agreement are signed by heads of clinical departments to operate changes in their services when required.

### Inclusion/exclusion criteria and recruitment

We will include all adult level I–III trauma centers in the Québec *Trauma Care Continuum* (*n*= 30). All centers will be recruited as the trial will be embedded in the 2023 evaluation cycle of the provincial trauma quality assurance program, which is mandatory [43]. Level IV centers will not be included as most see fewer than 20 trauma patients per year. Patient-level inclusion criteria will be all adult (> 16 years of age) admissions with a primary diagnosis of injury to any of these trauma centers. Admissions with a primary diagnosis of thermal injuries, foreign bodies, drowning, or late effects of injuries will be excluded as diagnostic and therapeutic approaches for these diagnoses are distinct [44].

### Intervention development

The multifaceted intervention was developed using extensive background work, conducted according to recommended steps for de-implementation [16, 45, 46]. First, we identified 63 potentially low-value practices through a scoping review and clinician survey [47]. Second, we synthesized evidence on the benefits, harms, and cost-effectiveness of these practices [48–51]. Third, we measured their incidence using trauma registry data [37]. Fourth, two panels of international experts (76% participation) and local stakeholders (94% participation) and three patient–partners (75% participation) reached an evidence-informed consensus on 16 practices that should be targeted for de-implementation [52]. Fifth, we derived quality indicators for 12 of these practices with trauma registry data and showed that 6 had moderate to high validity [36]. These quality indicators target (i) initial diagnostic imaging (head, cervical spine, or whole-body computed tomography [CT] in low-risk patients), (ii) specialist consultation (neurosurgical consult for mild traumatic brain injury and spine service consult for isolated transverse process fractures), and (iii) repeat imaging for transfers (repeat scan in patients with no disease progression and no additional details needed). Based on this work, we developed a multifaceted intervention with clinical and implementation science experts, patient–partners, and accreditation professionals using *UK Medical Research Council guidelines for the Development of Complex Interventions* (Additional file 3: Figure S1) [53, 54]. We matched frequently reported barriers and facilitators reported by experts in our consensus study [52] and documented in a knowledge synthesis [19] to implementation strategies using the *Consolidated Framework for Implementation Research (CFIR)-Experts Recommendations for Implementing Change (ERIC) tool* (Additional file 3: Table S2) [45, 55, 56].

### Trial interventions

Trial interventions will be delivered by research team members twice over two evaluation cycles (12 months per cycle with a refinement phase in the first cycle; Additional file 3: Fig. S1, Table S3).

The intervention group will receive the multifaceted intervention (Additional file 3: Table S4, Figures S2.1 & S2.2), which includes (1) refinement with end users; (2) an A&F report sent to local governing authorities presenting the following: performance compared to peers (simple A&F), a summary message indicating if action is required and a list of potential actions; (3) educational materials (a clinical vignette; consequences of the practice; links to practice guidelines, clinical decision rules and shared decision-making tools; a case review tool); (4) virtual educational meetings with the local trauma medical director, trauma program manager and data analyst on how to use the report and the case review tool and how to assess their barriers and facilitators to prepare their own action plan with the CFIR-ERIC matching tool [57]; and (5) two virtual facilitation visits 2 and 4 months after the transmission of the report (or at more appropriate times depending on needs) to support committees in preparing their action plan.

In line with recommendations [54] and to avoid contamination, we have embedded the refinement phase in the intervention (Additional file 3: Figure S1, Table S3, Fig. 1). We will first conduct four 60-min focus groups with 8–10 local trauma committee members [58] in trauma centers randomized to the intervention arm (stratified by designation level), with additional focus groups to obtain informational redundancy if required [59]. We will use a semi-structured interview guide (Additional file 3: Table S5) to gather reactions to the prototype, generate ideas on potential modifications, and identify other potential barriers and facilitators using the CFIR[60]. Second, we will recruit 5–8 end users [61] in the intervention arm and not involved in the previous phases to test intervention usability using a *Think Aloud Protocol *[62, 63]. We will use a one-to-one approach asking participants to articulate their reactions and their understanding of the information while going through the A&F report and the educational materials. We will modify the intervention in the presence of problems considered important by end users (e.g., difficulty in interpreting quality indicators) or in the presence of more minor problems (e.g., aesthetic details regarding the presentation of materials) reported frequently (by ≥ 5/8 end users). We will repeat this process with 5–8 additional end users until no major or frequent problems remain [61]. The intervention will be refined iteratively across focus group and usability testing rounds. We will strive for equal representation of males and females for focus groups and usability testing. Participation in this stage will also be balanced for clinical experience (i.e., < 2, 2–10, > 10 years) and disciplines (e.g., surgery, emergency medicine, radiology, critical care, nursing, management).

**Fig. 1 Fig1:**
[figure not shown]
Implementation over two evaluation cycles

The control group will receive the quality improvement intervention currently in place in the *Québec Trauma Care Continuum* (i.e., simple A&F report presenting their performance compared to peers on quality indicators measuring adherence to *high-value* care and risk-adjusted outcomes) with the addition of quality indicators on low-value care (already planned for the 2023 evaluation cycle). Simple A&F was chosen for the control because it is standard practice in the *Québec Trauma Care Continuum *and in most integrated trauma systems and the effectiveness of simple A&F for de-implementation has been studied [12].

### Randomization, allocation, blinding, and adherence

Centers will be randomized to simple A&F (control) or the multifaceted intervention (intervention) in a 1:1 ratio. An independent statistician at the Ottawa Methods Center (outside of the province in which the trial will be conducted and fully independent from the sites) will generate the allocation sequence using the covariate-constrained allocation technique [64] to ensure that study arms are balanced for designation level (I/II and III), cluster size, and the pre-intervention measure of the primary outcome. The allocation sequence will only be revealed on trial initiation. An independent INESSS professional will allocate centers to their randomization group. Local trauma committees will not be told explicitly what aspect of the intervention is randomized; they will only be aware that there are two variations of the intervention. Data extractors and data analysts will be blinded to group allocation. Due to the nature of the intervention, it will not be possible to blind the investigators to allocation groups. To minimize non-adherence and contamination, only participants in the intervention arm will participate in the refinement phase. We do not envisage major problems with adherence because quality assurance activities are mandatory in line with designation requirements [43].

### Outcome measures

Our primary outcome is low-value initial diagnostic imaging, calculated as the proportion of low-risk patients who receive head, cervical spine, or whole-body CT in the emergency department (Additional file 3: Table S6). This indicator was selected on consultation with our advisory committee as it applies to the most patients, is considered to have the greatest consequences in terms of adverse effects (unnecessary radiation, delays in care, incidental findings) and resource use (availability of CT scans, staff workload, costs), and is a good indicator of global overuse in a trauma system [36]. Secondary outcomes are low-value specialist consultation (neurosurgical and spine) and repeat imaging for transfers. Other secondary outcomes are mortality, complications, resource use (intensive care unit [ICU] and hospital length of stay), and unintended consequences (unplanned readmission, missed injuries); determinants for successful implementation of the intervention (process evaluation); and incremental cost-effectiveness ratios (economic evaluation).

Follow-up will be based on continuous data collection at each site, which is mandatory in line with designation requirements. Sites will be followed up over the 18-month interval (6 to 24 months) after implementation over two evaluation cycles using these data (Fig. 1, Additional file 3: Table S3). Our advisory committee recommended evaluation over two cycles as identifying problems, implementing solutions and operating change takes place over more than one cycle [65]. We will allow for a 6-month lag period post-implementation in the first cycle, corresponding to the time allotted to centers to submit an action plan. Because data collection is mandatory in all centers, we do not anticipate any loss to follow-up.

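### The single month 6 to 24 outcome window leaves the harm outcomes without a stated between-arm comparison for months 0 to 6

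*Protocol article*

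**What the plan says.** The Outcome measures section names low-value initial imaging as primary, then the other low-value-care outcomes, and continues: "Other secondary outcomes are mortality, complications, resource use" and "unintended consequences (unplanned readmission, missed injuries". Its next paragraph gives one window for follow-up: "Sites will be followed up over the 18-month interval (6 to 24 months) after implementation over two evaluation cycles using these data". The reason for starting at month 6 follows: "We will allow for a 6-month lag period post-implementation in the first cycle, corresponding to the time allotted to centers to submit an action plan".

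Trial interventions describes two cycles, "12 months per cycle with a refinement phase in the first cycle". The intervention arm receives a report with a message on whether action is needed, educational materials that include decision rules and a case review tool, educational meetings, and "two virtual facilitation visits 2 and 4 months after the transmission of the report". The same sentence lets the visits move to other times as needed.

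Outcome measures and Study data both say that registry collection is mandatory, and the former that it is continuous. The end of the Background lists effects on clinical outcomes and unintended consequences as separate secondary objectives.

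**The concern.** A lag is sensible for the primary outcome: counting months before a center has organised its response would dilute the effect. That argument does not carry over to harm. If an intervention center begins to withhold scans soon after the report arrives, a patient whose injury is missed in month 3 was treated at an exposed, randomized center, yet falls outside the stated window.

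Nothing else described in the article fills the gap with numbers. Trial management states that there will be no data monitoring committee. Process evaluation asks about unintended consequences, but through interviews in 20 centers shortly before each cycle ends, which yields recollections and not event rates by arm. The Discussion plans to upscale across Canada if the intervention proves effective and cost-effective, so the harm comparison should say what happened in the first months of exposure.

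**Working it through.** **1. Does any section give harm its own window?** Outcome measures gives one window and attaches it to no particular outcome. Study data gives the source of the harm data but no dates. Data analysis plan says binary secondary outcomes are handled like the primary one, and plans trend models over 6-month intervals without saying whether months 0 to 6 are among them; months 6 to 24 already make three such intervals. Sensitivity analysis adds no window. So the text shown contains no separate harm window.

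**2. What reaches intervention centers in months 0 to 6?** Setting gives centers 6 months from receipt of the report to submit an action plan, and the lag is described as "corresponding to the time allotted to centers to submit an action plan". The natural reading is that month 0 is about when the report is sent. The visits at months 2 and 4, if held as planned, then fall inside the lag.

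**3. The plan's own power figure.** Inputs from Sample size calculations: 15 clusters per arm, m = 285 per cluster-period, 0.14 versus 0.105, within-period ICC 0.044, cluster autocorrelation 0.984, two-sided 5%.
- Design effect of one period: 1 + 284 × 0.044 = 13.496.
- Before-after correlation of cluster means: 285 × 0.044 × 0.984 / 13.496 = 0.914.
- Baseline-adjusted (ANCOVA) design effect: 13.496 × (1 − 0.914²) = 2.214 with the unrounded correlation. Effective n per arm: 15 × 285 / 2.214 = 1,931. Power 0.913.
- Change-score design effect: 13.496 × 2 × (1 − 0.914) = 2.313. Effective n per arm 1,848. Power 0.901.

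The stated 90% is reproduced. It does not change if the primary outcome keeps months 6 to 24.

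**4. Size of the gap.** Assumption: a cluster-period is 18 months, as the historical observation periods and the follow-up interval are.
- Time: 6 / 24 = 25% of post-implementation time.
- Patients per center: 285 × 6 / 18 = 95.
- Per arm: 95 × 15 = 1,425. Overall: 95 × 30 = 2,850.

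These are low-risk patients eligible for the primary outcome. The article does not give the number of all eligible admissions, nor any rate of missed injury, readmission or death, so no number of omitted events follows.

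**5. What would the extra months add in precision?** A 24-month window gives 380 patients per center (285 + 95), a third more. The article gives no ICC for harm, so the primary outcome's values serve as an illustration.
- Post-period only: design effect 1 + 379 × 0.044 = 17.676; effective n per arm 15 × 380 / 17.676 = 322.5, against 15 × 285 / 13.496 = 316.8. Standard error ratio √(316.8 / 322.5) = 0.991, about 1% smaller.
- With baseline adjustment (ANCOVA, baseline still 285): effective n per arm 2,164 against 1,931. Ratio √(1,931 / 2,164) = 0.945, between 5% and 6% smaller.

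The case for the early months therefore rests on seeing the period at all, not on precision.

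**The case against.** The strongest reply is that months 6 to 24 is a defensible main harm window. The early components go to governing authorities, trauma leads and committees, and the visits are there to help prepare an action plan. Setting describes change as coming through local protocols and department agreements, and Outcome measures says it takes more than one cycle. Control centers also receive low-value-care indicators. The contrast between arms before month 6 may thus be small, and pooling those months into the main harm analysis could pull the estimate toward no difference, the wrong direction for a safety comparison. This stands, and it is why the main window should not be replaced.

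Other parts of the reply also stand. Visit timing is flexible. The refinement phase sits in the first cycle, and its position relative to month 0 depends on Fig. 1. The lag applies equally to both arms, so it creates no imbalance between them and does not breach intention-to-treat. Harm from lasting imaging restraint would continue into the analysed months; only an excess confined to the start would be missed.

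What does not stand is that the matter is merely left to another document. The article states one window with one reason, and that reason does not address harm.

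**Conclusion.** The point holds as a modest, inexpensive improvement. As the text reads, harm in months 0 to 6 enters no stated between-arm comparison, although intervention contact is planned in that period and the registry will hold the data. The gap is 25% of post-implementation time, about 2,850 primary-outcome patients if accrual is 285 per center per 18 months.

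A reader might infer more, and the document does not support it:
- That clinicians withhold scans from the first report onward, or that early restraint is the riskiest. The text supports early delivery to centers; how far bedside practice changes by then is unknown.
- That early harm is certainly counted nowhere. Fig. 1 and Table S3, which the window sentence cites, are not shown, and the 6-month trend models could include the period.
- That a third more patients means a third more information. At the primary outcome's ICC and autocorrelation the standard error falls by roughly 1% to 6%.
- That harm events are being lost in a known number. No harm rates are given.

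**What to change.** Keep months 6 to 24 as the main window for effectiveness and for harm. Add to Outcome measures a prespecified by-arm comparison of mortality, complications, unplanned readmission and missed injuries over months 0 to 6, reported separately beside the 6 to 24 result. State what month 0 is, for example transmission of the first report. Show pooled months 0 to 24 as supplementary only, with a note that it may dilute a harm signal. If Fig. 1, Table S3 or the analysis plan already provides for this, a cross-reference is enough.

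The cost is one or two sentences and one extra registry extract period; no new data collection is needed, and the primary analysis and its power are unchanged. The early estimate will be imprecise and should be presented as such: a wide interval for months 0 to 6 is not evidence that there was no harm.
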